### Randomization and blinding

Randomization sequence will be generated by computer [38], and three groups with blocks of 12 participants will be considered. This stage will be conducted by a researcher not involved in the study. This researcher will keep the randomization list confidential until the end of the study and will organize the allocation in sequentially numbered opaque envelopes. These envelopes will be sealed, and the randomization sequence will be according to the coding that will be created for study groups (control, experimental 1, and experimental 2).

The content of each envelope will be revealed only at the beginning of the training of each patient by study therapists in order to maintain allocation confidentiality. The same therapists involved in control group training will perform training in the experimental groups. Sample characterization measures and outcome measures will be evaluated by masked researchers in relation to group allocation. These researchers will be the same as those who enrolled participants in the study.

Only variables that will be collected during the training will be evaluated by study therapists (non-blind). Statistical analysis will be performed by one researcher, who will be blind to the allocation of patients in groups. Data will be tabulated with a predetermined encoding by another blinded evaluator, who will also check data (range check for data values). The present protocol has been prepared in accordance with relevant items from the SPIRIT (Standard Protocol Items: Recommendations for Interventional Trials) checklist (Additional file 1) and the SPIRIT figure (Fig. 1).

**Fig. 1 Fig1:**
[figure not shown]
Schedule of enrollment, interventions, and assessments. *Abbreviations*: *BP* systemic arterial blood pressure, *HR* heart rate, *HRsub* submaximal heart rate, *t1* 1st week, *t2* 2nd week, *t3* 3rd week, *t4* 4th week, *t5* 5th week, *t6* 6th week, *t1month* short-term follow-up, *t12months* long-term follow-up, *tpost6* post-training

## Measures

### Sample characterization measures

Clinical and demographic data: These will be evaluated by filling out a structured identification form about data such as paretic side, stroke type, age, gender, injury time, and drug treatments (including beta-blockers).Ability to walk: This will be evaluated by FAC, which consists of a sensitive and reliable instrument for gait evaluation in stroke patients with hemiparesis [33]. FAC ranks six levels of walking ability according to the amount of physical support required for this task. On this scale, the score can vary from 0 (unable to walk or needs the help of two therapists) to 5 (independent in locomotion).Motor function: It will be evaluated by Fugl–Meyer Scale, which allows us to analyze and quantify sensory-motor function after stroke [39]. Only motor function requirements will be used in this study, and it includes measuring movement, coordination, and reflex activity of the shoulder, elbow, wrist, hand, hip, knee, and ankle. Scores below 50 points indicate severe motor impairment; 50–84, outstanding; 85–95, moderate; and 96–99, mild [40].

### Outcome measures

Primary outcome measures considered for this study are the following:Gait speed: This will be measured by the 10-meter walking test [41]. This test consists of a simple measure which presents good reliability and reproducibility and is valid to evaluate physical mobility in a clinical or home environment [42].Functional capacity: This will be measured by the 2-min walk test [43]. This test has demonstrated adequate inter- and intra-examiner reliability in patients with stroke and has an advantage compared with the 6- and 12-min walk tests because it presents a time considered efficient and reduces fatigue effects in these patients [44].Cardiovascular parameters: BP will be checked by using a calibrated digital arm sphygmomanometer (Visomat Comfort III^®^, Incoterm, São Paulo, Brazil) on the non-paretic arm. HR will be measured by means of an HR meter (chest belt) (Polar Care^®^, Polar, São Paulo, Brazil). Derived variables such as mean BP, reserve HR, and predicted maximum HR will be calculated from BP and HR measured values. Physiological measures such as BP and HR are non-invasive parameters easily verified by using available devices in clinical practice. Exercise HR has been used as a physical fitness measure after stroke [45], and both HR and BP have been indicated to evaluate the cardiovascular response to exercise in individuals with stroke [14]. Also, peripheral oxygen saturation will be checked by using a pulse oximeter (Palpus 1 SA210, Rossmax, Taipei, Taiwan). Exercise capacity (energy expenditure) in metabolic equivalents (METs) will be estimated from HR by using the HR index (HR_INDEX_) in accordance with the equation developed by Wicks *et al*. [46] for patients with and without heart disease (including those taking beta-blockers).

Secondary outcome measures considered for this study are the following:Neuromuscular torque: Quadriceps muscle isometric torque peak of both lower limbs will be measured by using an isokinetic dynamometer (Biodex Multi-Joint System 3 pro^®^, Biodex Medical Systems, Shirley, NY, USA). The isokinetic dynamometer is considered a gold standard in muscular strength evaluation and is used to evaluate isometric torque peak and force in patients with stroke [47, 48]. Torque peak will be obtained with patients performing five isometric contractions of knee extension, interspersed with 30 s of rest, counting only the contraction which obtains the highest torque value. Each contraction should last 5 s, and the first and last seconds are not counted in the measurement.Quality of life: The assessment of quality-of-life perception will be performed through a quality-of-life assessment scale in stroke (Stroke-Specific Quality of Life Scale, or SS-QoL) [49]. This scale has 49 items distributed in 12 domains (energy, family role, language, mobility, mood, personality, self-care, social role, reasoning, upper limb function, vision, and work/productivity). It is valid and reliable in assessing quality of life after stroke, including in the Brazilian population [50].

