### Sample size

Sample size was calculated by using an online calculator [31], and the variable gait speed (in meters per second) was adopted as the primary outcome measure. According to a previous study involving individuals with post-stroke hemiparesis who performed treadmill training with partial weight support and anterior inclination of 10° (experimental) and no inclination (control) [26], standard deviations observed in the experimental and control groups were 0.1 and 0.2, respectively. The sample size was calculated from these data to detect a difference in gait speed between the groups of 0.18 m/s (α = 5% and power = 80%) since the minimum detectable difference in the gait speed for patients with chronic stroke was 0.18 m/s [32]. A ratio between the control and experimental groups of 1:2 was considered, as it was verified that the smallest numbers needed to detect the expected difference would be 8 individuals in the control group and 16 individuals in the experimental group, totaling 24 participants. Given a dropout rate of about 40%, a sample total of 36 participants (12 in the control group and 24 in the experimental group) was determined.

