## Statistical analysis

Data analysis will be carried out by a blinded evaluator regarding group allocation by using the Statistical Package for the Social Sciences software (SPSS, IBM, Armonk, NY, USA) for Windows. Only the main study researcher (not involved in data collection) can make the final decision to stop the trial and will have access to the final data.

Descriptive analysis of the sample characterization variables will be performed through central tendency and dispersion measures. Inferential analysis will consider statistical significance of 5% for all studied variables. Mixed analysis of variance (ANOVA) with repeated measures will be used to compare values and variations of outcome measures, comparing values between groups and between baseline, post-training, and follow-up assessments. Normality tests (Shapiro–Wilk) will be used for outcomes and will be compared between groups within each training session by using intergroup comparisons, *t* tests for independent samples, or Mann–Whitney tests.

Group description will be presented as mean and standard deviation, and the effect size and the 95% confidence interval will be reported. Intention-to-treat analysis will be performed for dropout data, considering the last data obtained from the participant.

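### The sample size has one primary outcome, gait speed, but the outcome section makes three domains and about ten variables primary, each tested at 5% with no hierarchy

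*Protocol article*

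**What the plan says.** Three sections of the protocol article bear on this.

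- **Sample size.** One outcome is primary: "the variable gait speed (in meters per second) was adopted as the primary outcome measure". The 8 control and 16 experimental participants, and the 36 to be enrolled, come from gait speed alone. No assessment time is named.
- **Outcome measures.** The list begins "Primary outcome measures considered for this study are the following" and has three domains. After gait speed comes functional capacity: "This will be measured by the 2-min walk test". The third domain, cardiovascular parameters, covers blood pressure (BP) and heart rate (HR). It adds "Derived variables such as mean BP, reserve HR, and predicted maximum HR will be calculated from BP and HR measured values", then "peripheral oxygen saturation will be checked by using a pulse oximeter", and finally "Exercise capacity (energy expenditure) in metabolic equivalents (METs) will be estimated from HR". A separate list of secondary outcomes follows (quadriceps torque and quality of life), so the primary label is deliberate.
- **Statistical analysis.** "Inferential analysis will consider statistical significance of 5% for all studied variables". Outcomes are compared between groups and across baseline, post-training and follow-up by mixed repeated-measures ANOVA. No hierarchy, division of alpha or rule for declaring success is given.

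**The concern.** A reader cannot tell which result decides the trial. By the Sample size section it is gait speed. By the Outcome measures section it could be any of about ten variables, and the analysis rule lets each be declared significant at 5%. If gait speed shows nothing but, say, oxygen saturation or diastolic BP falls below 0.05, the plan as written allows that to be reported as a positive primary outcome. The error rate over the set of primary outcomes is then above 5%, and the sample size supports none of them except gait speed.

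**Working it through.** **1. The plan's own figure.** Inputs from the Sample size section: difference 0.18 m/s, SDs 0.1 (experimental) and 0.2 (control), alpha 5%, power 80%, ratio 1:2.

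- Allocation-weighted variance: (0.2² + 2 × 0.1²)/3 = 0.02, so SD = 0.141.
- Control n, two-sided: (1 + 1/2) × 0.02 × (1.960 + 0.842)²/0.18² = 7.27, rounded up to 8. Experimental n = 16, total 24.

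The stated 8 + 16 is reproduced with one outcome, one comparison and the full 5%. This pooled form is one of several possible; using the SDs unpooled as assigned gives 11 + 22. That is a separate matter, but in every form only gait speed enters.

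**2. Count of primary variables.** (1) gait speed, (2) 2-minute walk, (3) systolic BP, (4) diastolic BP, (5) HR, (6) mean BP, (7) reserve HR, (8) predicted maximum HR, (9) oxygen saturation, (10) METs. The split of BP is an inference: the outcome list says only BP, while the exclusion criteria refer to systolic and diastolic values. Predicted maximum HR is fixed by age if it follows the 220 − age form used in the exclusion criteria. It then cannot respond to treatment, which leaves nine.

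**3. Chance of at least one false positive, one 5% test per variable, no true effects.** The documents give no correlations, so all correlations below are assumed.

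| Reading | Assumption | Chance |
|---|---|---|
| Three domains, one test each | independent: 1 − 0.95³ | 14.3% |
| Nine variables | independent: 1 − 0.95⁹ | 37.0% |
| Nine variables | equal correlation 0.3 (simulated) | 32.6% |
| Nine variables | equal correlation 0.5 (simulated) | 27.1% |

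**4. Keeping the built-in dependence.** Mean BP follows from systolic and diastolic BP, METs are estimated from HR, and change in reserve HR mirrors change in resting HR if maximum HR is age-predicted. A mixed ANOVA was simulated with three groups of 12 and four assessments, testing only group-by-time for each of the nine variables (20,000 trials per setting). METs were modelled, as a further assumption, with equal weight on resting and exercise HR.

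| Gait speed with 2-minute walk | Systolic with diastolic | All other measured pairs | Chance |
|---|---|---|---|
| 0 | 0 | 0 | 30.8% |
| 0.7 | 0.6 | 0 | 28.4% |
| 0.7 | 0.6 | 0.2 | 27.7% |
| 0.8 | 0.7 | 0.3 | 26.3% |
| 0.8 | 0.7 | 0.5 | 24.0% |

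**5. Could every outcome stay primary with adjustment?** Using the formula and SD of step 1 with Bonferroni:

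- Three domains, alpha 0.05/3 = 0.0167: 10 + 20 = 30 evaluable, against 24 planned.
- Nine or ten variables, alpha 0.0056 or 0.005: 13 + 26 = 39 evaluable, more than the 36 to be enrolled.

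**The case against.** The strongest reply is that the plan sets a 5% level per variable and never claims a family-wise rate, and that adjustment is often left to an analysis plan, which is not at hand. That is fair as to silence on adjustment, and the absence of a multiplicity method alone would not be a finding. It does not remove the conflict between a single primary outcome in one section and a plural list in another, nor the 5% rule, which is stated and covers every variable.

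The reply also stands on the numbers. A reader might take 27–37% as the trial's error rate. The documents do not support that: they give no correlations, and the 37% end needs independence, which variables derived from BP and HR cannot have.

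A reader might go further and multiply by three post-baseline visits and three pairwise t tests. The plan does not say this. Outcomes across assessments go into one mixed ANOVA, and the t and Mann–Whitney tests are for comparisons within a training session.

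Nor does the sample size already settle on the post-training assessment, as might be inferred; it names no time point.

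Finally, the research questions are cardiovascular as well as functional, so making every cardiovascular outcome secondary has a real scientific price. A pre-stated hierarchy would be a legitimate way to keep such claims.

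**Conclusion.** The concern holds as a contradiction between the Sample size and Outcome measures sections, made consequential by the 5% rule in the Statistical analysis section. What counts as a positive trial is not defined, and the chance of at least one false primary result is above the nominal 5% on every reading examined.

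The size is illustrative and assumes one test per variable. The most realistic figure is about 24–31%, for nine variables with their derivation from BP and HR respected. The equicorrelated range of 27–37% is a simpler approximation. The lenient count of three independent domains gives 14%, still nearly three times nominal (14.3/5 = 2.9). The contradiction itself depends on none of these assumptions.

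**What to change.** Through a documented amendment, made before unblinding:

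1. In Outcome measures, make gait speed the sole primary outcome, consistent with the Sample size section.
2. Name one primary time point. Post-training is a natural candidate, but the choice has to be made now because the plan does not contain it.
3. Name one primary test or contrast. The combined inclined groups against control would match the 1:2 comparison used for the sample size.
4. Move the 2-minute walk, all cardiovascular variables, and gait speed at the other time points to secondary, reported with estimates and 95% confidence intervals. If any of them is to support a claim, use Holm's procedure or a pre-stated hierarchy.
5. In Statistical analysis, limit the 5% rule to match.

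The work is a wording change, but data collection began in August 2017, so it needs a dated amendment with its reason. The substantive cost is that cardiovascular and 2-minute walk results can no longer be presented as primary. Keeping them all primary with Bonferroni adjustment is not a realistic alternative at this sample size, as step 5 of the working shows.

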### Participant monitoring measures

Participants will be monitored during interventions by not only cardiovascular parameter variables but also the following variable:Perceived effort and pain: Quantification of perceived effort and pain will be used as indicators to monitor exercise tolerance. They will be verified through the CR-10 (Category-Ratio Scale) Borg Scale [51], modified by Foster *et al*. [52] (2001).

## Evaluation procedures

The researchers will be trained before data collection procedures to ensure the reliability of measurements. It is important to highlight that these researchers will remain blind to group allocation throughout the study period.

Previously contacted patients with stroke or those who spontaneously search for the study will be evaluated according to inclusion criteria at our laboratory, where they will be informed about the research objectives and procedures to be carried out. Once they agree to participate in the study, they will be asked to sign a consent form.

The participants will first be submitted to a general approach to obtain clinical, demographic, and anthropometric data, and other measures of sample characterization will also be collected. Furthermore, the following outcome variables will be evaluated: gait speed, functional capacity, and muscle torque. Participants will subsequently remain at rest, sitting for at least 15 min. During this period, quality of life will be evaluated. Lastly, cardiovascular parameters will be obtained (at rest).

Outcome measures will be collected again at the end of the interventions (post-training), after 30 days of the end of the interventions (short-term follow-up), and after 1 year of the end of the interventions (long-term follow-up). Adverse events will be evaluated at follow-up.

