Thus, there is a strong need to design, implement, and evaluate training protocols which include functional activities—such as gait, walking up or down stairs, and ramps—to improve the cardiovascular condition of individuals with neurological pathologies, particularly stroke. Since treadmill training may influence functional and especially cardiovascular outcomes of individuals with a prior health condition, it is important to consider these variables in evaluating post-stroke training protocol effects. Also, Mehrholz *et al*. [29], in a recent systematic review, suggest further studies including different intensities (such as inclination) for treadmill training after stroke, as improved walking speed and endurance had no long-term benefits. In this context, the following questions arise: (1) Does inclined treadmill training promote cardiovascular and functional parameters in individuals with chronic stroke, and is it effective and safe for these patients when compared with treadmill training without inclination? (2) If inclined treadmill training promotes these parameters, what level of treadmill inclination is the most effective for improving cardiovascular and functional variables of individuals with chronic stroke?

The proposal of the study is to investigate whether treadmill inclination influences functional and cardiovascular parameters compared with treadmill gait without inclination and whether there are differences in effects on cardiovascular or functional parameters (or both) according to the degree of treadmill inclination during gait training.

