**Fig. 2 Fig2:**
[figure not shown]
System for gait training: Gait Trainer System 2

The training protocol will follow what was used in a previous study, involving patients with subacute stroke, since the protocol used was safe and capable of increasing gait speed and distance covered on a treadmill [53]. In the first training session, participants will undergo a few minutes of treadmill training for familiarization and will be instructed to hold onto the anterior treadmill bar with their non-paretic hand to provide stability. The treadmill speed will be selected as the “maximum comfort”, meaning the maximum tolerated by the individual, while adequate posture is maintained throughout gait cycle without any compensation or muscle fatigue.

From the second session, participants will be encouraged to withdraw support from their non-paretic hand over the treadmill bar. In the following session, participants will be encouraged to increase the treadmill speed according to individual tolerance. Participants will be encouraged to achieve maximum speed at the beginning of the session. After reaching that speed, it will remain constant throughout the session. This procedure will be repeated at the beginning of all subsequent sessions.

The treadmill training sessions will last 30 min, and two small rest periods (about 3 min) will be allowed in the 10th and 20th minutes, which will not be counted in the total duration of the session. During these pauses, the therapists will monitor cardiovascular parameters, effort perception, and pain. However, HR will be monitored throughout the session so as not to exceed the maximum submaximal values (75% of maximum frequency) and so that training can occur by maintaining target frequency of 50% of maximum HR [14].

Before training (in rest), individuals will be assessed regarding cardiovascular parameters and will be reassessed in the 1st and 5th minutes after the end of the session by the study therapists. The control group will be submitted to training by treadmill during a 30-min session without inclination three times per week for 6 weeks.

Experimental group 1 - treadmill gait training with inclination of 5%

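### The only stated timing for adverse-event evaluation is follow-up, 30 days and 1 year after training ends, although comparative safety during training is part of research question 1

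*Protocol article*

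**What the plan says.** The Background section sets out two research questions. The first asks of inclined training: "is it effective and safe for these patients when compared with treadmill training without inclination". The Discussion expects the trial to yield a resource that can be called safe.

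Under Evaluation procedures, outcomes are measured again at three points: post-training, then "after 30 days of the end of the interventions (short-term follow-up") and "after 1 year of the end of the interventions (long-term follow-up"). The next sentence is "Adverse events will be evaluated at follow-up". It is the only sentence in the article that uses the term adverse events. They are not listed among the primary or secondary outcomes.

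Training itself is observed. Participant monitoring measures states: "Participants will be monitored during interventions by not only cardiovascular parameter variables but also the following variable", which is perceived effort and pain. It gives the purpose of that addition: "Quantification of perceived effort and pain will be used as indicators to monitor exercise tolerance". The training description under Study groups adds, for the two rest periods in each session: "During these pauses, the therapists will monitor cardiovascular parameters, effort perception, and pain". Heart rate is also watched throughout, and cardiovascular parameters are taken before each session and 1 and 5 minutes after it.

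The Sample size section enlarges 24 participants to 36 with the words "Given a dropout rate of about 40" percent.

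**The concern.** A risk that comes from walking on an incline arises while participants are walking on it, during the 6 weeks of training. The stated evaluation of adverse events falls after that period, by at least a month. Two kinds of loss may follow. A participant who stops training because of an event may never attend the visit at which events are evaluated. A participant who does attend must recall events from one to several months earlier, or over a year earlier at the last visit.

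At stake is the safety half of research question 1. If one arm has more training-related events, and those events lead to withdrawal, that arm could also lose more of its events from the record. The comparison could then look more even than it is, and a statement that inclined training is safe would rest on those who stayed.

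**Working it through.** **Timing, by setting the sections side by side.**

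1. Exposure: 6 weeks × 3 sessions = 18 sessions per participant (Abstract; Study groups).
2. Meaning of follow-up: Evaluation procedures, the Abstract and the legend of Fig. 1 all name post-training separately and attach the follow-up label to the 1-month and 1-year visits. On the article's own usage, the first stated adverse-event evaluation is 30 days after the last session.
3. Objective: comparative safety, incline against flat (Background).
4. What sessions record: heart rate, blood pressure and other cardiovascular parameters, effort and pain. Effort and pain are given a tolerance purpose; the cardiovascular parameters are primary outcomes. The article does not say that any of these readings is classified or counted as an adverse event. Falls, injuries, interrupted sessions and reasons for withdrawal are not among the variables.

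So the stated evaluation in (2) does not match the exposure in (1) and the objective in (3), and (4) fills the gap only in part.

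**How many participants might not reach the 1-month visit.** Inputs: 36 participants, 12 per arm, about 40% dropout, 24 needed before dropout (Sample size).

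- The plan's own figure: 24 / (1 − 0.40) = 40 and 24 × 1.40 = 33.6, so neither gives 36. The loss that 36 allows for is (36 − 24) / 36 = 33.3%. Both rates are therefore carried forward.
- At 40%: 0.40 × 36 = 14.4, about 14 in all; 0.40 × 12 = 4.8, about 5 per arm, leaving about 7.
- At 33.3%: 12 in all, 4 per arm, leaving 8.

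The article does not say when dropout is expected. These counts apply only if all of it falls before the 1-month visit, so they are upper bounds.

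**What an arm with no recorded events could support.** The exact upper limit for zero events in n is 1 − a^(1/n), with a = 0.05 for a one-sided 95% limit and a = 0.025 for the upper end of a two-sided 95% interval.

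| n observed | one-sided | two-sided |
|---|---|---|
| 12 | 1 − 0.05^(1/12) = 22% | 1 − 0.025^(1/12) = 26% |
| 8 | 1 − 0.05^(1/8) = 31% | 1 − 0.025^(1/8) = 37% |
| 7 | 1 − 0.05^(1/7) = 35% | 1 − 0.025^(1/7) = 41% |

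**Chance of seeing any affected participant in an arm.** Assume, for illustration, a true risk of 10% per participant and dropout unrelated to events. The chance is 1 − 0.9^n: 72% for n = 12, 57% for n = 8 and 52% for n = 7. Dropout caused by events would lower the last two further.

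**The case against.** The strongest reply is that the sentence does not say that events are evaluated at follow-up and at no other time, and that the article condenses a fuller protocol. Session forms and withdrawal logs are commonly kept there. The assessment schedule in Fig. 1 is not visible, though its legend lists weekly time points during training, and the SPIRIT checklist is a separate file. A reader might infer that adverse events are evaluated at follow-up only; the text does not support that word. What can be said is that follow-up is the only timing stated.

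A reader might also infer that training-period events would be lost, or that 36 × 18 = 648 sessions leave no record. Neither is supported. Physiological readings, effort and pain are collected at every session, and the Statistical analysis section plans comparisons between groups within each session. Therapists are present, participants are telephoned to confirm each session and evaluation, and the Discussion promises assistance to anyone harmed, which implies that harms would be noticed. An event can also be reported in retrospect at 1 month. Nor does the tolerance purpose extend to heart rate and blood pressure.

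All of this stands, and it narrows the point. It does not remove it. The article does not merely leave timing to another document: it states a timing, and that timing lies outside the exposure period. Noticing a harm is not the same as recording it by arm, and the session readings leave out falls, injuries, interruptions and withdrawal reasons.

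It is also fair to say that adverse events are not a listed outcome, so no planned test is affected. But safety is part of a stated research question, and an answer to it needs data from the training weeks.

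**Conclusion.** The point holds in this form: the stated timing of adverse-event evaluation does not fit the safety question, and training-period events could be under-ascertained, especially in participants who leave before the 1-month visit. The number at risk of contributing no adverse-event evaluation is at most about 14 of 36 (40% dropout) or 12 of 36 (33%). Reading either as an expected count would go too far, since some dropout may fall between 1 month and 1 year, after events have been asked about once.

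Bias toward no difference is plausible, not certain. It requires that event-related withdrawal differs by arm and that those events go unrecorded.

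The small sample is a separate limit that better timing does not cure. Even with all 12 in an arm observed and no events, a risk of up to 22% (one-sided) or 26% (two-sided) remains compatible with the data. The plan should be changed on this point; if the full protocol already records events at each session, correcting the one sentence is enough.

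**What to change.** Reconcile the safety question in the Background, Participant monitoring measures, Evaluation procedures and the training description under Study groups. Replace the sentence on adverse events with wording to this effect:

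- Therapists record adverse events at every session, including falls, injuries, interrupted sessions and abnormal in-session readings, together with the reason for each withdrawal.
- Participants are asked about events again at post-training, 1 month and 1 year.
- The report gives, by arm and among all randomised participants, the number with at least one event and the number of events, with exact confidence intervals for the proportions.
- The report states that 12 participants per arm cannot establish safety.

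The cost is one added line on the session record and one table. Therapists already attend every session, and no training or clinical rule changes. The downside is a more modest safety conclusion.
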